#### Outcomes Assessment

A research assistant who is blinded to the participant’s treatment condition will email the participant a link to a web-based survey containing the outcome measures. If a participant fails to complete the survey within 48 hours of receipt, they will receive up to 3 reminders through email, voicemail, and SMS text messaging. Though participants will not be compensated for completing the intervention, they will be compensated US/CAD $10 (or its equivalent depending on their location) for each postintervention survey completed (postintervention +8 biweekly follow-up surveys) and an additional US/CAD $20 for each of the 2 postintervention interviews, for a maximum total of US/CAD $130, to maximize the chances that even those participants who abandoned the intervention prematurely will complete the outcome surveys.

#### Statistical Analyses

Descriptive statistics will examine treatment acceptability outcomes as well as the trial recruitment rate. A 2-tailed *t* test will be used to compare the treatment arms in terms of baseline characteristics, assessing randomization success. A mixed model design using the MIXED procedure in SAS (version 9.4; SAS Institute) applying an intent-to-treat approach will compare the intervention arm to the waitlist control group in terms of FertiQoL, PHQ-9, GAD-7, Copenhagen Multi-Center Psychosocial Infertility Fertility Problem Stress Scale, and Relationship Assessment Scale (RAS) score across the 9 outcome measurement points (ie, at the end of intervention week 7 and biweekly for 16 weeks). Each outcome will be examined in a separate model; subject will be treated as a random effect, and the treatment assignment will be treated as a fixed effect. A repeated statement will identify assessment week as a repeated measure factor. Baseline levels of the outcome will be included as a covariate. This method has been shown to provide optimal statistical power relative to measuring pre- and postintervention outcome change [36]. In using all available data, a mixed model design has also been shown to outperform ad hoc approaches, such as the last-outcome-carried-forward approach [37].

In addition to examining the main effect of treatment assignment on outcomes, the interaction between assignment and assessment week will be examined to determine whether outcomes are maintained across the 9 postintervention measurements. Sensitivity analyses will use a similar approach to examine potential treatment moderators: membership in the LGBTQIA+ communities, baseline FertiQoL score, cultural background, disability status, and pursuit of conception through medical intervention.

The LOGISTIC procedure will assess the occurrence of mood (major or minor depressive episode or persistent depressive disorder) and/or anxiety disorders (generalized anxiety disorder, social anxiety disorder, or panic disorder) in the 2 treatment arms at the posttreatment assessment as well as at the 16-week follow-up.

To limit the family-wise error rate, the Benjamin and Hochberg [38] false discovery rate correction will be applied to all analyses.

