### Randomization Scheme

The Clinical Research Support Unit at the University of Saskatchewan will create the randomization scheme and provide the principal investigator with opaque envelopes containing treatment assignments, ensuring that the research team has no control over the assignments. Randomization will take place at the end of each enrollment session, after the baseline surveys have been completed, and will be stratified based on whether a woman is undergoing fertility treatments or attempting to conceive without medical intervention, as this will be a potential moderating variable.

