#### Power Calculations

Power calculations were performed using G*Power (Axel Buchner) and are focused on the primary outcome, infertility-related quality of life. Based on SDs observed in the population of distressed women with infertility [18], setting α at .05 and power at 80%, a total of 128 participants would be needed to detect a moderate effect size (Cohen *f*=0.25), equivalent to a 6-point difference on the FertiQoL (out of 100) between 2 arms. To allow for a 25% (42/170) dropout rate, we will recruit 170 participants (85 per arm), in line with average completion rate of 82% observed in our meta-analysis of psychological interventions for infertility-related distress and allowing for additional drop-out given considering the 16-week follow-up.

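### Randomisation is stratified by fertility-treatment status but the stated mixed model omits the stratum; if it predicts outcome beyond baseline, the reported standard error is slightly too large

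*Protocol article*

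**What the plan says.** Under Randomization Scheme, allocation "will be stratified based on whether a woman is undergoing fertility treatments or attempting to conceive without medical intervention", and the reason given is "as this will be a potential moderating variable".

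Under Statistical Analyses, the model for FertiQoL and the other continuous outcomes is set out term by term. First, "subject will be treated as a random effect, and the treatment assignment will be treated as a fixed effect". Then "A repeated statement will identify assessment week as a repeated measure factor", and "Baseline levels of the outcome will be included as a covariate". A treatment-by-week interaction is added to see whether effects last over the 9 post-intervention assessments. The stratification factor is not among these terms. What appears to be the same variable comes up only in the next paragraph, in a list of five possible moderators that ends "cultural background, disability status, and pursuit of conception through medical intervention".

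The LOGISTIC analysis of mood and anxiety disorders is described without any covariates.

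**The concern.** Stratified randomisation balances the arms on the stratification factor. That balance lowers the true sampling variance of the treatment estimate when the factor is related to outcome. A model without the factor does not recognise this: it counts the between-stratum variation as residual noise, and its standard error describes a trial in which the arms could have differed on that factor. The confidence interval is then wider than it needs to be and the test rejects less often than its nominal level.

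At stake is a small amount of power on the primary outcome, which the sample size supports at 80% with almost no margin. Timing also matters. Under Protecting Against Sources of Bias, the article commits to reporting in line with the original protocol and to justifying any departure. A stratum term is better written in now than explained later.

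**Working it through.** **Reproducing the plan's figure.** The article states: "setting α at .05 and power at 80%, a total of 128 participants would be needed", for Cohen f = 0.25, equated with 6 FertiQoL points.
- For two equal arms, d = 2f = 0.5, so the implied SD is 6/0.5 = 12 points.
- The noncentrality parameter is N·f² = 128 × 0.0625 = 8. The F test on 1 and 126 degrees of freedom has power 0.8015; N = 126 gives 0.795. The 128 is reproduced (the 5% level is taken as two-sided).
- 128/0.75 = 170.7, against 170 stated. This is reproduced to within rounding.
- The calculation credits neither the baseline covariate nor the stratum, so 128 and 170 stand whichever model is used.

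**Effect of omitting the stratum.** Let R² be the share of the outcome variance left after baseline adjustment that the stratum explains. The documents do not give it, so it is an assumption and is varied from 0. With treatment balanced within strata:
- reported SE / correct SE = 1/√(1 − R²)
- actual type I error = 2[1 − Φ(1.96/√(1 − R²))]
- with n = 64 per arm, reported SE = √(2/n) and correct SE = √(2(1 − R²)/n), in SD units
- power, stratum omitted = 1 − Φ((1.96 × reported SE − 0.5)/correct SE)
- power, stratum included = 1 − Φ(1.96 − 0.5/correct SE)

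If the strata split evenly, the stratum gap that produces a given R² is g = √(R²/[(1 − R²) × 0.25]) residual SDs. The points column takes the residual SD as 12.

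| Assumed R² | Gap g (points) | SE ratio | Type I error | Power, omitted | Power, included |
|---|---|---|---|---|---|
| 0 | 0 (0) | 1.000 | 5.0% | 80.7% | 80.7% |
| 0.01 | 0.20 (2.4) | 1.005 | 4.9% | 80.9% | 81.1% |
| 0.02 | 0.29 (3.4) | 1.010 | 4.8% | 81.0% | 81.5% |
| 0.05 | 0.46 (5.5) | 1.026 | 4.4% | 81.4% | 82.7% |
| 0.10 | 0.67 (8.0) | 1.054 | 3.9% | 82.0% | 84.6% |

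The first row shows 80.7% rather than 80.15% because these are large-sample formulas. Power with the stratum omitted never falls below that row, so the loss is a gain forgone and not a shortfall against plan.

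**Simulation check.** A single-outcome ANCOVA was simulated as a simplification of the nine-visit mixed model: N = 128, SD 12, exact balance within strata, 4000 runs per setting. Baseline–outcome correlation was 0.5 or 0.7 and strata were split 50/50 or 70/30 (all assumed). Gaps here are in units of the SD of 12.
- Stratum difference carried wholly by baseline: SE ratio 1.000.
- Residual gap 0.2 SD: SE ratio 1.006 to 1.009.
- Residual gap 0.5 SD: SE ratio 1.034 to 1.059; type I error 3.7% to 5.0%; power 0.8 to 1.7 points lower.
- The closed form agrees. At correlation 0.7 and a 50/50 split, 0.5 SD is 6 points and the residual SD is 12 × √(1 − 0.49) = 8.57, so g = 0.70 and the ratio is √(1 + 0.25 × 0.49) = 1.059.
- In that setting the actual spread of the treatment estimates was 1.523 without the stratum term and 1.520 with it, while the average reported SE was 1.609 and 1.519. The estimate is equally precise either way; only the reported SE differs.

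**The case against.** - **Baseline adjustment may already do the work.** A quality-of-life difference between people in and out of treatment at entry is what the baseline covariate absorbs, and then the SE ratio is 1.000. This stands, and it is why the point is conditional. The Introduction describes the burden of fertility treatment but does not compare the two strata, before or after baseline adjustment.
- **The factor was chosen as a moderator and is used as one.** True, and a moderator need not be prognostic. But the moderator analysis does not alter the standard error of the main treatment comparison.
- **The gaps needed for a visible effect are large.** A residual gap of 0.5 SD is 6 points on the plan's scale, the whole effect the trial is powered to detect. This stands, so the lower rows of the table are the less likely ones.
- **A separate analysis plan may add the term.** It may. But the article does not leave the model open: it lists the random, fixed and repeated terms and the covariate.

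A reader might infer that omitting the stratum throws away the precision of the stratified design. The documents and the check do not support that: balance still protects the estimate, and only its reported standard error is conservative. A reader might also carry the standard-error argument over to the LOGISTIC models. It does not transfer: adding a prognostic factor there changes the odds ratio being estimated and does not shrink its standard error as in a linear model.

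**Conclusion.** The point holds as a minor, conditional one. The design stratifies, the stated model leaves the stratum out, and the direction of any error is conservative. With partial R² between 0 and 0.05 the standard error is overstated by 0% to about 3% and power is 0 to about 1.3 points lower than it could be; at 0.10, about 5% and 2.6 points. These sizes rest on an assumed prognostic strength, on arms balanced within strata, and on a single-outcome approximation to the repeated-measures model. It would be too strong to say that the standard error is too large as a matter of fact, because no figure in the article shows that the stratum predicts outcome once baseline is in the model.

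**What to change.** Add the randomisation stratum (undergoing fertility treatment, yes or no, as recorded at randomisation) as a fixed effect in each MIXED model. Keep the stratum-by-treatment interaction for the moderator analysis. The cost is one model term and one degree of freedom; the variable is already needed for allocation, and no sample-size figure changes. If the stratum is not prognostic, almost nothing is lost.

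For the LOGISTIC models this is a separate choice. If the stratum is added there, state that the odds ratio is then conditional on it.

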### Protecting Against Sources of Bias

A number of strategies will be used to protect against bias. First, the trial will be registered with clinicaltrials.org before any data collection commences. Second, as described above, the randomization scheme will be created by a third party, and the study research assistants will be instructed to strictly adhere to the randomization protocol without exception. Third, though it is not possible to maintain full blinding of either the participant or research team given the nature of the intervention, all outcomes will be collected by a research assistant who is blind to the participant’s treatment allocation. Fourth, an intent-to-treat approach will be taken in analyzing the results—every effort will be made to continue to collect outcome data on all participants, regardless of whether participants dropped out of the intervention early or not. Final, we will follow the CONSORT-SPI (Consolidated Standards of Reporting Trials for Social and Psychological Intervention Trials) reporting guidelines [23] in reporting the results of the trial, strictly adhering to the original trial protocol. Any deviations will be clearly described and justified.

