### Primary and Secondary Outcomes

#### Overview

Self-reported psychological outcomes will be assessed immediately postintervention (ie, at the end of the 7th week) and every 2 weeks for 16 weeks. Mood and anxiety disorders will be assessed immediately postintervention as well as 16 weeks postintervention. Finally, health care use will be assessed at postintervention week 16. The control group will follow an identical outcome assessment schedule.

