#### Secondary Outcomes

Secondary outcomes will include depressive and anxious symptoms, instances of mood and anxiety disorders, relationship quality, and health care use. Treatment adherence and acceptability will also be assessed.

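### Run as written, the logistic analysis of mood and anxiety diagnoses uses only interviewed participants, which falls short of the plan's general intent-to-treat commitment

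*Protocol article*

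**What the plan says.** All references are to the protocol article.

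- **Endpoint.** Diagnoses are secondary (Secondary Outcomes: "Secondary outcomes will include depressive and anxious symptoms, instances of mood and anxiety disorders, relationship quality, and health care use"). They come from a structured interview held twice, both times after the intervention (Primary and Secondary Outcomes, Overview: "Mood and anxiety disorders will be assessed immediately postintervention as well as 16 weeks postintervention"). No baseline interview is listed.
- **Analysis.** Statistical Analyses: "The LOGISTIC procedure will assess the occurrence of mood" and/or anxiety disorders "in the 2 treatment arms at the posttreatment assessment as well as at the 16-week follow-up". Nothing is said there about participants without an interview.
- **General principle.** Protecting Against Sources of Bias: "an intent-to-treat approach will be taken in analyzing the results—every effort will be made to continue to collect outcome data on all participants", whether or not they stop the program early.
- **Continuous outcomes.** Statistical Analyses ties intent-to-treat to the mixed models and defends them for using all the data available. Neither statement is repeated for the diagnoses.
- **Expected loss.** Power Calculations: "To allow for a 25% (42/170) dropout rate, we will recruit 170 participants (85 per arm").
- **Interview as a separate contact.** Outcomes Assessment pays for the surveys and, separately, "an additional US/CAD $20 for each of the 2 postintervention interviews".

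**The concern.** The article sets one standard for missing data on the continuous scales and names a procedure without that property for the diagnoses. A mixed model uses every observed score of a participant who misses some visits. A plain logistic regression at one time point uses nothing from a participant who has no interview then, even if that person returned the PHQ-9 and GAD-7 in the same week. No baseline diagnosis is listed that could serve as a covariate.

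Missingness could plausibly differ by arm. Only the intervention arm has a program to abandon, and only the control arm is offered the program once the study is complete, which is a reason to stay. If intervention participants who still have a disorder are the ones who skip the interview, the disorder rate in that arm is understated. The Discussion predicts lower rates in the treatment arm, so an error in that direction would look like confirmation.

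**Working it through.** **1. The plan's own figures.** With Cohen f = 0.25, alpha .05 and N = 128, the two-group F test has 80.1% power, so the stated 128 reproduces. Dropout inflation: 128 / 0.75 = 170.7, or 171 against the stated 170. Also 42/170 = 24.7% and 170 − 42 = 128. The sample size is sound and is not at issue.

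**2. Participants the logistic model would use.** The 25% is a trial dropout allowance set for the primary outcome. If it also applied to the 16-week interview (an assumption), about 42 of 170 would have no diagnosis. A plain fit would then use about 128, or 64 per arm.

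**3. When the odds ratio is biased.** Let p be the true disorder rate in an arm, r1 the share of cases interviewed and r0 the share of non-cases interviewed.

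Observed odds = p·r1 / [(1 − p)·r0] = true odds × (r1/r0)

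Observed OR = true OR × (r1/r0 in intervention) / (r1/r0 in control)

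The bias is the ratio of the two retention ratios. It vanishes if retention is unrelated to diagnosis in both arms, or related in the same way in both.

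**4. Illustration with no true effect.** These inputs are assumptions, because the article gives no disorder rate by arm and no dropout mechanism. The true rate is set at 35% in both arms, inside the 30%-40% that the Introduction gives for clinical symptoms (a proxy, not a diagnosis rate). Control retention is 75% regardless of diagnosis. Intervention retention is about 75% overall but differs by diagnosis.

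| Cases interviewed | Non-cases interviewed | Overall | Observed rate, intervention | Apparent OR |
|---|---|---|---|---|
| 70% | 78% | 75.2% | 32.6% | 0.70/0.78 = 0.90 |
| 65% | 80% | 74.75% | 30.4% | 0.65/0.80 = 0.81 |
| 60% | 83% | 74.95% | 28.0% | 0.60/0.83 = 0.72 |

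Middle row in full: 0.35 × 0.65 = 0.2275; 0.65 × 0.80 = 0.52; sum 0.7475; 0.2275/0.7475 = 30.4%, against 35.0% in control.

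For a pattern very close to the middle row (35% of cases and 19.6% of non-cases lost), simulation with 64 interviewed per arm gave a two-sided type I error of about 9%. With missingness unrelated to diagnosis it was about 5%.

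**5. The same link in both arms.** Take true rates of 20% and 35%, with 60% of cases and 80% of non-cases interviewed in each arm. True OR = (0.20/0.80)/(0.35/0.65) = 0.464. Observed OR = (0.12/0.64)/(0.21/0.52) = 0.464. There is no bias.

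**6. Direction.** The formula is symmetric. Moving the 65%/80% pattern to the control arm gives 1/0.8125 = 1.23 under no effect. Nothing in the article fixes the direction.

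**7. What the missing interviews could hide.** With 22 cases among 64 interviewed of 85 in one arm, the rate among all 85 lies between 22/85 = 25.9% (no missing person is a case) and (22 + 21)/85 = 50.6% (all are).

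**The case against.** A reader might infer that the plan drops everyone without an interview and so turns intent-to-treat into an analysis of program completers. The article does not support that.

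- It never says that such participants are dropped. This follows from the procedure's default, and the same procedure can be run on imputed data.
- Someone who stops the program but is interviewed stays in the assigned arm. The article explains intent-to-treat as continued data collection after program dropout, and its payments are meant to retain such people. The result is an available-case analysis by assigned arm.
- Leaving the program and missing the interview are different events. Either arm can miss interviews, and no text shows that the link with diagnosis differs by arm. The retention splits above are invented.
- Missing-data handling for one secondary binary endpoint is often left to an analysis plan, which is not shown here.
- Imputation is not a full cure. The article describes the PHQ-9 as paralleling major depressive disorder and the GAD-7 as paralleling generalized anxiety disorder. The endpoint also covers minor and persistent depression, social anxiety and panic disorder. On the stated schedule, a person lost before week 7 has no post-baseline scores.

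The first three points stand and limit the claim to a conditional one. The fourth lowers the weight but does not dispose of the matter: the article does name a method for this endpoint, and that method, run as written, is weaker than the principle and the reasoning the same article states. The fifth stands as a limit on the remedy.

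**Conclusion.** The point holds in limited form. As written, the diagnosis analysis is an available-case comparison by assigned arm, of about 128 of 170 participants if interview loss matches the planned 25%. It falls short of the general intent-to-treat commitment and of the case made for the mixed models.

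Bias is possible but not shown. It requires a link between missing interviews and diagnosis that differs by arm. Under no true effect, the assumed patterns give apparent odds ratios of 0.72 to 0.90. The size rests on the assumed 35% rate, the assumed retention splits, and the transfer of the 25% allowance to the interviews. The concern is confined to a secondary endpoint and leaves the primary analysis untouched. It is still worth correcting, because a better analysis is available from data the trial already plans to collect.

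**What to change.** State that the main analysis of diagnoses includes all randomized participants. Multiply impute missing diagnoses at posttreatment and at 16 weeks, separately by arm, from baseline and biweekly PHQ-9, GAD-7 and FertiQoL scores and the other interview, and then fit the logistic model. Keep the available-case logistic regression as supportive. Report interview completion by arm. Add a simple sensitivity analysis in which the imputed odds of disorder are shifted by arm, to cover departures from missing at random.

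The likely gain: in a simulation with no true effect, with intervention-arm missingness driven by earlier symptom scores (assumed settings), available-case logistic regression gave an odds ratio of about 0.76 with type I error of 10-12%. Multiple imputation from the repeated scores and the earlier interview gave about 0.99 with 4-5%, without loss of precision. The gain will be smaller if missingness depends on the unobserved diagnosis itself.

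The cost is analysis wording, some programming and a slightly longer report; no new data are needed. The drawback is reliance on an imputation model. Three scales on ten occasions (baseline plus nine) make 30 candidate scores for 85 people per arm, so the predictors should be reduced in advance, for example to the scores nearest each interview.

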**Methods:**

We will recruit 170 individuals struggling to become pregnant in Canada or the United States to be randomized to our 7-week self-help program or a treatment-as-usual condition. The primary outcome will be fertility quality of life, while secondary outcomes will include depressive symptoms, anxious symptoms, and relationship quality, assessed before and after the program as well as biweekly for 16 weeks following completion of the program. Self-reported health care use and the presence of diagnosed mood and anxiety disorders, assessed through a structured psychiatric interview, will also be assessed immediately following the intervention and at the 16-week follow-up assessment. Treatment adherence and retention will also be recorded throughout the intervention. Multilevel modeling will compare the intervention arm to the treatment-as-usual condition in terms of all continuous outcomes across the 9 measurement points. Logistic regression will be used to assess the occurrence of mood and anxiety disorders in the 2 treatment arms at the posttreatment assessment as well as at the 16-week follow-up. Sensitivity analyses will examine potential treatment moderators: membership in the LGBTQIA+ (lesbian, gay, bisexual, transgender, queer, intersex, and asexual) communities, baseline fertility quality of life, cultural background, disability status, and pursuit of conception through medical intervention.

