## Methods

### Trial Design

The proposed research is a single-blind randomized controlled trial comparing the above-described self-help program to a waitlist control condition. As the project requires no in-person contact, we will recruit women living throughout Canada and the United States. Fertility quality of life, infertility-related distress, symptoms of depressed mood and anxiety, and relationship quality will be assessed before and after the program, as well as every other week for 16 weeks.

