#### Participant Screening and Enrollment

Prospective participants will be emailed the link to a web-based eligibility survey. If found to be eligible, they will be asked to provide their contact information, and a research assistant will contact them to schedule an enrollment session through videoconference.

During the Zoom-facilitated remote enrollment session, eligibility will be confirmed, a brief introductory video explaining the study and intervention will be presented, and consent will be obtained. An enrollment session in which visual contact is made will ensure that our recruited participants are not simply “bots” posing as eligible participants. During the session, participants will complete the baseline questionnaires through a link emailed to them by the research assistant. Upon completion of the questionnaires, the research assistant will open an opaque envelope, revealing the participant’s random assignment to either the treatment or control condition. The research assistant will then ask the participant which day of the week they would like to receive their weekly module video (if assigned to the treatment condition) or weekly outcomes survey (if assigned to the control condition).

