#### Participant Safety

Participants endorsing suicidal ideation on question 9 of the PHQ-9 at baseline will be permitted to participate in the study but will be informed that their level of risk will be reassessed weekly. Specifically, each week, they will receive a survey question, “Please pick out the one statement that best described how you have been feeling during the past week, including today: (A) I don’t have any thoughts of killing myself. (B) I have thoughts of killing myself, but I would not carry them out. (C) I would like to kill myself, or (D) I would kill myself if I had the chance.” If participants choose either C or D, a message including contact information for 2 suicide hotlines will appear. As well, an automatic notification will be sent to the study therapist, flagging the response. They will then follow up with the participant immediately by phone, at most within 24 hours. If participants endorse A or B, they will simply be allowed to continue with the program.

In addition, the presence of active suicidal ideation (presence of a plan or intent) will be assessed by the researcher during the Zoom-facilitated enrollment session. Those endorsing active suicidal ideation will be referred to additional in-person mental health resources available in their geographic area. They will be given access to the program for their own benefit but will not be enrolled in the study.

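### The logistic comparison of mood and anxiety disorders names no baseline covariate, and the plan's baseline-adjustment rule cannot reach it; adding covariates already collected would recover some power

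*Protocol article*

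**What the plan says.** Statistical Analyses describes two kinds of model. For the continuous scores it specifies mixed models in some detail, including "Baseline levels of the outcome will be included as a covariate", and defends that choice on grounds of power. For diagnoses it says only "The LOGISTIC procedure will assess the occurrence of mood" and/or anxiety disorders in the two arms at two times. No covariate is named there.

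On timing, the outcomes Overview says "Mood and anxiety disorders will be assessed immediately postintervention as well as 16 weeks postintervention". The abstract says that "the presence of diagnosed mood and anxiety disorders, assessed through a structured psychiatric interview, will also be assessed immediately following the intervention", with a second interview 16 weeks later, whereas the self-report scales are measured before and after the program. Outcomes Assessment offers "an additional US/CAD $20 for each of the 2 postintervention interviews". At enrollment the article describes questionnaires: "During the session, participants will complete the baseline questionnaires through a link emailed to them by the research assistant". No baseline diagnostic interview appears anywhere.

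Baseline symptom scores do exist. Trial Design says "symptoms of depressed mood and anxiety, and relationship quality will be assessed before and after the program", and Participant Safety relies on a baseline PHQ-9: "Participants endorsing suicidal ideation on question 9 of the PHQ-9 at baseline will be permitted to participate in the study". Randomization Scheme stratifies by whether the participant is having fertility treatment.

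**The concern.** The rule that each model adjusts for its own baseline value has nothing to act on when the outcome is a diagnosis, since no baseline diagnosis is described. Unless a substitute is named, the natural default is a two-arm comparison without covariates. The article values baseline adjustment for the continuous outcomes because it raises power, and the same reasoning is not carried to the binary endpoint. The trial was sized for FertiQoL alone, so power for diagnoses is likely to be limited. The article nevertheless expects lower disorder rates in the treated arm (Significance of the Study), and a null result there would be hard to interpret.

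There is also a smaller matter of wording. No criterion keeps out people who already have a mood or anxiety disorder, so a diagnosis found after treatment may be new or persisting. *Occurrence* can be read as new onset, which these data cannot show.

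**Working it through.** **1. Number analysed.** Power Calculations gives Cohen f = 0.25, α = .05, power 80%, 128 participants, and 170 recruited. In two groups f = 0.25 is d = 0.5, so 6 points implies an SD of 6/0.5 = 12. The noncentral t gives power 0.7952 at 63 per arm and 0.8015 at 64, so 128 reproduces. For dropout, 128/0.75 = 170.7, and 170 × 0.75 = 127.5. The sample size stands, and 64 per arm is used below.

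**2. Assumptions.** The article gives no diagnosis rates. The control rate of 35% is the middle of the 30%-40% with clinical *symptoms* cited in the Introduction, which is not a SCID rate. The treated rate of 20% has no source in the article. The correlation r between a baseline symptom score and the later liability to disorder is also assumed, at 0.3, 0.5 or 0.7.

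**3. Unadjusted power by formula.** Mean rate = (0.35 + 0.20)/2 = 0.275.

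z = [0.15 × √64 − 1.96 × √(2 × 0.275 × 0.725)] / √(0.35 × 0.65 + 0.20 × 0.80) = (1.200 − 1.238)/0.6225 = −0.06

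Power = Φ(−0.06) ≈ 0.476.

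**4. Simulated gain from adjustment.** 64 per arm, 3,000 replicates per row, two-sided test at 1.96, one baseline score, disorder defined by a threshold on a latent scale.

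| Control vs treated | r | Power unadjusted | Power adjusted | Gain (points) |
|---|---|---|---|---|
| 35% vs 20% | 0.3 | 0.483 | 0.505 | 2.2 |
| 35% vs 20% | 0.5 | 0.473 | 0.537 | 6.4 |
| 35% vs 20% | 0.7 | 0.480 | 0.622 | 14.2 |
| 40% vs 20% | 0.3 | 0.710 | 0.728 | 1.8 |
| 40% vs 20% | 0.5 | 0.686 | 0.744 | 5.8 |
| 40% vs 20% | 0.7 | 0.693 | 0.837 | 14.4 |
| 30% vs 15% | 0.3 | 0.537 | 0.559 | 2.2 |
| 30% vs 15% | 0.5 | 0.529 | 0.577 | 4.8 |
| 30% vs 15% | 0.7 | 0.534 | 0.673 | 13.9 |

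A separate simulation of the full model proposed below (two symptom scores plus the stratum) at 35% vs 20% gave about 50%, 54% and 65% at r = 0.3, 0.5 and 0.7, against 48% to 50% unadjusted. Its type I error was about 5-6%.

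**5. Validity.** With 35% in both arms, the rejection rate in the one-score simulation was 0.049 to 0.057 unadjusted and 0.053 to 0.055 adjusted. The mean risk difference was essentially zero either way.

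**6. Where the gain arises.** At 35% vs 20%:

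| r | Log OR (SE) unadjusted | Log OR (SE) adjusted | SD of risk difference, unadjusted → adjusted | Variance ratio |
|---|---|---|---|---|
| 0.3 | −0.795 (0.416) | −0.844 (0.432) | 0.0763 → 0.0749 | 1.04 |
| 0.5 | −0.795 (0.416) | −0.943 (0.460) | 0.0769 → 0.0717 | 1.15 |
| 0.7 | −0.791 (0.416) | −1.174 (0.524) | 0.0787 → 0.0666 | 1.40 |

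The SE of the log odds ratio rises, but the conditional estimate moves further from zero. At r = 0.5 the ratio goes from 0.795/0.416 = 1.91 to 0.943/0.460 = 2.05. On the risk-difference scale the estimate stays at −0.151 and its spread falls.

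**7. Persisting disorder.** If prevalence is the same at baseline and follow-up in controls, the share of follow-up cases already present at baseline is P(above threshold both times)/prevalence under a bivariate normal. For prevalence 30% to 40% and r = 0.3 to 0.7 this runs from 0.427 to 0.694. At 35% and r = 0.5 it is 0.561.

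**The case against.** The strongest reply is that the article is silent here: it never says the logistic model is unadjusted. Covariates for a secondary outcome are often left to an analysis plan, and that plan is not shown. This stands, so a reader should not infer that the authors have decided against adjustment. What remains is that the one rule they state cannot be applied to diagnoses, so a substitute has to be named somewhere.

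A reader might also infer that pre-existing disorder, or chance imbalance in it, biases the comparison. The documents do not support that. Randomisation makes presence at follow-up a fair contrast, the standard error already allows for chance imbalance, and the simulated error rates agree. Nor is counting persisting disorder a fault in a treatment trial, since remission is part of the benefit sought.

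Nor does the article claim to measure new onset. The abstract uses both *presence* and *occurrence*, and the Discussion speaks of rates.

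The absence of a baseline interview is inferred. The Overview leaves out the baseline visit for the self-report scales as well, and payments cover only contacts after the intervention. The abstract's contrast between the two sets of outcomes is the better evidence.

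Finally, the power figures rest on assumed rates, and the larger gain needs a strong correlation. About 22.4 + 12.8 = 35 events for four parameters besides the intercept is roughly 9 each, which is thin. The full-model simulation kept its error rate near nominal, so this does not defeat the proposal.

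**Conclusion.** The point holds as a minor one. The logistic analysis of disorders names no covariate, and the stated baseline rule cannot supply one. The comparison is valid as it stands. What it may give up, at 64 per arm and an assumed 35% vs 20%, is about 2 points of power at a baseline-outcome correlation of 0.3, 6 at 0.5 and 14 to 15 at 0.7, starting from about 48%. At those rates adjustment does not bring power to 80%. The figures use a nominal two-sided .05 test, and the false discovery rate correction planned for all analyses could only lower them.

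It would be wrong to say that precision is lost on every scale: the SE of the log odds ratio goes up with adjustment, and the benefit lies in the test and in the risk difference. Low power here also contradicts nothing in the article, which makes a power claim for FertiQoL only.

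**What to change.** Add to Statistical Analyses, unless the analysis plan already has it: *The logistic models at each time point will include baseline PHQ-9, baseline GAD-7 and the randomisation stratum (fertility treatment yes/no). A standardised (marginal) risk difference, obtained by averaging predicted probabilities over all participants under each arm, will be reported with the odds ratio.*

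The risk difference is needed because the adjusted odds ratio is conditional on the covariates and is not comparable with an unadjusted one.

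Replace *occurrence* with *presence*, in line with the abstract's description of the outcome. Separating onset from persistence would need a diagnostic interview at baseline. That is an extra procedure, and this repair does not require it.

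The cost is a sentence or two and no new data. The covariates should be fixed before outcomes are seen, so that they cannot be chosen afterwards.
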